**6.2 NF-PNEN management**

NF-PNEN management will be decided at the hospital and all therapeutics decision will be decided/coordinated by the treating physician.

Advised surveillance strategy consists of imaging studies (MR or EUS or US), every 6 months for the first two years and yearly thereafter for five years in the absence of significant changes on imaging or symptoms appearance. During surveillance, a high-quality imaging technique (MRI or CT) is mandatory at least every 12 months.

Determination of CgA during follow-up is at physician’s discretion. During follow-up, the treating physician is responsible for patient management and decision-making. If follow-up parameters change during follow-up, the decision for a more diagnostic work-up, surgery, or an intensified follow-up schedule is at the discretion of the treating physician (**Appendix 2**). If surgical resection is warranted, timing and type of resection will be established by the treating physician. Suggested scheme of follow up after surgery is depicted in **Appendix 3.**

Date of surgery does not change the timing of follow up which starts from the date of enrolment. If during surveillance a NF-PNEN size increases > 2 cm and surgery is not performed, the reason should be stated. In this case patient is not excluded and follow-up will continue regularly.

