# METHODS

## Study Endpoints

### Main study endpoint

### The primary endpoint is disease/progression-free survival, defined as the time from study enrolment to the first evidence of progression (surveillance group) or recurrence of disease (surgery group) or death from disease.

### Secondary study endpoints

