### NF-PNEN evolution, in terms of development of symptoms, tumour growth, development of distant metastases and secondary pancreatic duct dilatation.

### The perceived burden of surveillance or follow-up after surgery for participants, as assessed by questionnaires regarding attitude towards surveillance and general anxiety and depression (Hospital Anxiety and Depression scale, HADS[^22^](#_ENREF_22)). Moreover we ask patients to fill out EORTC QLQ-C30 (version 3) and EORTC QLQ-GI.NET21 Module.

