# STATISTICAL ANALYSIS

The first analyses will regard the data collected within the first 2 years. This report will contain purely descriptive statistics, according to the study endpoints described. The second analysis, after 5 years, will give an update of the first report and provide a more in depth analysis of the primary and secondary study endpoints.

Baseline patient and NF-PNEN characteristics will be described. Also, descriptive of the primary and secondary endpoints will be given. Depending on distributional properties of the observed variable, percentages, means ± standard deviation (SD), or medians with interquartile ranges (IQR) will be reported. Statistical significance will be assessed with use of the Student’s t-test for normally distributed continuous data; either the chi-square test for categorical data (with Yates’ correction when appropriate) or Fisher exact test for categorical data; and the median test for non-normally distributed continuous data. All reported p-values will be two-sided and a value < 0.05 will be considered to be significant. Data will be analysed with SPSS (SPSS Inc, Chicago, Illinois). For the primary endpoints, univariate comparisons will be conducted, to identify individual patient and NF-PNEN risk factors for progression/recurrence. As primary potential risk factors are considered; 1. NF-PNEN size at initial diagnosis, 2. NF-PNEN growth during follow-up, 3. serum CgA, 4.. Patient age, 5. Ki67.

Outcomes will be evaluated in the intention-to-treat population on the basis of treating physician-assessed tumor progression/recurrence. Survival analysis techniques and Cox regression with time-dependent recurrent covariates measures will be applied. Progression/recurrence is defined according to Response Evaluation Criteria in Solid Tumors (RECIST)[^23^](#_ENREF_23) version 1.0 criteria. In the surveillance group progression is defined as the appearance of distant metastases and/or local signs of invasiveness (I.e. vascular or nearby organs invasion). The mere tumor size increasing will be not considered a sign of progression unless it reaches > 2 cm of maximum diameter. The two groups of patients (active surveillance and surgical resection group) will not be directly compared. Rate of expect events is 0-10% for the two groups^19^ .

Multivariate survival analysis will only be performed if the number of events will be > 30. The potential risk factors, given above, will have first interest.

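### Resecting a surveillance patient at or below 2 cm is not a primary event and rules out the later size event, so surveillance progression-free survival cannot be read without data on conversion to surgery

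*Protocol*

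**What the plan says.** **Primary endpoint (protocol section 7).** Time runs from enrolment to the "first evidence of progression (surveillance group) or recurrence of disease (surgery group) or death from disease". The event type depends on the group, and conversion from surveillance to surgery is not a component.

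**Progression under surveillance (section 8).** "In the surveillance group progression is defined as the appearance of distant metastases and/or local signs of invasiveness". On growth: "The mere tumor size increasing will be not considered a sign of progression unless it reaches > 2 cm of maximum diameter".

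**Surgery during surveillance (section 6.2).** If follow-up parameters change, "the decision for a more diagnostic work-up, surgery, or an intensified follow-up schedule is at the discretion of the treating physician". No threshold links this decision to the endpoint. The clock is unaffected: "Date of surgery does not change the timing of follow up which starts from the date of enrolment".

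**Analysis population (section 8).** "Outcomes will be evaluated in the intention-to-treat population on the basis of treating physician-assessed tumor progression/recurrence". The same section states that the two groups are not compared directly and gives the anticipated risk: "Rate of expect events is 0-10% for the two groups".

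**Secondary endpoints (section 7).** One covers patients with an indication for resection, including how many were operated on, morbidity, mortality and recurrence. Another covers "NF-PNEN evolution, in terms of development of symptoms, tumour growth, development of distant metastases and secondary pancreatic duct dilatation".

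**The concern.** Intention-to-treat normally means analysis by assigned treatment. Here nothing is assigned, so the term does not say where a patient belongs who starts under surveillance and is later operated on. That matters because the event differs between groups: progression in one, recurrence in the other.

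The endpoint also treats two similar courses differently. A lesion that grows from 11 to 19 mm and is then resected gives no event. A lesion left until it measures 21 mm gives one. Which of the two occurs depends partly on the centre's readiness to operate.

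Two results are at stake. The first is the surveillance progression-free estimate, which is central to the stated aim of evaluating the most appropriate management. The second is the risk-factor analysis: growth during follow-up is one of the five listed factors, and it is also a likely reason for resecting a lesion before it can become an event.

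**Working it through.** **Step 1: follow one patient through the rules.** Take a surveillance patient resected at 19 mm without metastasis or invasion.
- Metastasis or invasion before surgery: none, so no event.
- Size: section 8 also names RECIST 1.0, but its sentence on growth excludes growth alone up to 2 cm, so no event.
- Conversion: not in the section 7 definition, so no event.
- After surgery: the lesion is gone and the size event can no longer occur. Later metastasis or death from disease still counts. Whether local recurrence counts is unclear, because recurrence is the event of the surgery group.

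**Step 2: try the possible group rules.** The protocol fixes none of these.
- Kept in surveillance: one of the routes to an event is closed.
- Censored at surgery: the censoring is informative if growth prompted the operation.
- Moved to the surgery group from enrolment: the time before surgery is immortal for recurrence.

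Under none of them is conversion itself visible in the primary result.

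**Step 3: illustrate the size.** The protocol gives no conversion rate and no split of its target of at least 1000 patients, so every rate below is an assumption. The only figure to anchor to is the anticipated 0-10%.

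*Conversion linked to prognosis.* Let p be the underlying risk and q the share of would-be progressors resected first. If none of them later has a counted event, the observed risk is p × (1 − q). A hazard of 3% per year over 3.5 years gives p = 1 − exp(−0.03 × 3.5) = 0.0997.

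| q | observed, p = 10% | observed, p = 5% |
|---|---|---|
| 25% | 7.5% | 3.75% |
| 50% | 5.0% | 2.5% |
| 75% | 2.5% | 1.25% |

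If all 1000 patients were under surveillance, p = 5% and q = 50% would give 1000 × 0.05 × 0.5 = 25 events instead of 50. That is below the more than 30 events that section 8 requires for multivariate analysis.

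*Conversion unrelated to prognosis.* Use constant hazards over T = 5 years: a = −ln(1 − p)/T for progression and b = −ln(1 − c)/T for conversion, where c is the 5-year conversion risk. Incidence of progression first = a/(a + b) × [1 − exp(−(a + b)T)]. For p = 5% and c = 10%, a = 0.01026 and b = 0.02107. Per 1000 patients this gives:
- progression first: 47.5
- conversion first: 97.5
- either: 145.0

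Across p = 5% to 10% and c = 5% to 20%, progression first ranges from 45 to 98 per 1000 and either event from 98 to 280.

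**Step 4: compare.** Conversion unrelated to prognosis barely moves the progression figure (50 to 47.5 per 1000). Conversion driven by impending progression can halve it or more. A reader of the results needs to know how many converted, when and why.

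**Step 5: check whether the secondary endpoints supply this.** They count operated patients and describe growth, symptoms and duct dilatation. They do not separate conversions from upfront surgery or give time to conversion. Section 6.2 asks for a reason only when a lesion exceeds 2 cm and is not operated on.

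**The case against.** **A surveillance-first strategy may be exactly what is being estimated.** Section 6.2 builds surgery into surveillance and keeps follow-up running from enrolment. Read with intention-to-treat, that is a treatment-policy estimate, and fewer progressions because growing lesions were removed is then a result of the strategy. This stands. A reader might infer that the planned estimate is simply too low. That holds only if the target is the course of lesions never operated on, which the protocol does not claim.

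**Surveillance failures are not hidden.** Growth, symptoms, duct dilatation and operated patients are all secondary endpoints, and later metastasis or death from disease still counts. This stands too. What is missing is the split by upfront and converted surgery, and the timing.

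**A lesion resected after passing 2 cm has already had its event.** This is correct and limits how large q can be. Nothing in the documents shows that patients resected earlier were about to progress.

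**Competing-risk methods would not raise the progression estimate.** This is correct. Treating resection as a competing event in the example above again gives about 7.5%, 5.0% and 2.5%.

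**Censoring rules belong in the statistical analysis plan.** This stands for censoring, and the protocol prescribes none, so informative censoring cannot be charged to it. But the endpoint, the progression rule and the population are set in the protocol itself, and together they leave the converted patient undefined.

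**Conclusion.** The point holds in a limited form. As the protocol defines the endpoint, resection at or below 2 cm without metastasis or invasion counts as progression-free and rules out the size event. The surveillance estimate therefore depends partly on local readiness to operate. The growth risk-factor analysis is affected if growth prompts resection, which is likely but not documented.

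The effect cannot be sized from the documents. The fall from an assumed 10% to between 7.5% and 2.5% rests on an assumed hazard, an assumed 25% to 75% resected first, and no later counted event among those resected. It shows only that the effect could span much of the anticipated 0-10%. No figure stated in the protocol is contradicted. Because the groups are not directly compared, no planned treatment contrast is biased.

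**What to change.** 1. In section 8, replace the intention-to-treat population by: *all enrolled patients, grouped by the management plan recorded at enrolment (surveillance or upfront surgery)*.
2. Keep the primary endpoint and describe it for the surveillance group as the outcome of a surveillance-first strategy. Follow-up continues after conversion, and later recurrence, metastasis or death from disease counts.
3. Beside it, report the cumulative incidence of conversion to surgery before progression, with progression as the competing event, split by recorded reason. This describes conversion; it does not by itself correct the progression estimate.
4. Add a supplementary composite of progression or resection for growth, symptoms, duct dilatation or suspected invasion.
5. Ensure that the CRFs record intended management at enrolment and the reason for each resection. The CRF contents are not shown, so these items may already exist.

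The cost is protocol wording, a small extra analysis and at most a few CRF items. The composite will look less favourable for surveillance than the primary figure and itself depends on local surgical practice, so it should stay supplementary. None of this takes a position on when resection should be done.

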# BACKGROUND

Nonfunctioning pancreatic neuroendocrine neoplasms (NF-PNEN) are rare tumors that exhibit a wide heterogeneity of aggressiveness. The current World Health Organization (WHO) classification identified three categories of NF-PNEN (NF-PNEN-G1, NF-PNEN-G2, and NF-PNEC-G3) based on Ki-67 value [^1^](#_ENREF_1). Indications for surgery include the presence of a localized NF-PNEN in the absence of distant metastases as curative resection of these tumors is associated with favourable prognosis especially for low grade [^2-4^](#_ENREF_2).

In the last decade a dramatic increase in diagnosis of small, incidentally discovered, NF-PNEN was observed[^5^](#_ENREF_5) [^6^](#_ENREF_6). Several studies highlighted the role of incidental diagnosis as a powerful prognostic factor for NF-PNEN[^7^](#_ENREF_7) [^8^](#_ENREF_8). Moreover, other investigators observed a clear relationship between the tumor diameter and low risk of malignancy and systemic progression.[^9-11^](#_ENREF_9).

In particular, a tumor size ≤ 2 cm seems to be associated with a negligible risk of disease recurrence and with a very low incidence of aggressive features such as lymph node involvement[^4^](#_ENREF_4) [^12^](#_ENREF_12).

On this basis, the European Neuroendocrine Tumor Society (ENETS) proposed a “wait and see” approach for small NF-PNEN when incidentally discovered[^13^](#_ENREF_13). Since then, various series evaluated the safety of a conservative management for small, sporadic, incidentally diagnosed, NF-PNEN[^14-19^](#_ENREF_14).

After a median follow-up of 28-45 months, all the studies confirmed that an intensive surveillance for incidental and small NF-PNEN is safe in selected cases. None of the patients in the observational group deceased for disease or had disease progression when lesions were less than 2 cm. Nevertheless, available data are based only on retrospective series with a significant heterogeneity of inclusion criteria and different tumor diameter cut-off^14-18^ and the appropriate management of this entities (surveillance versus surgery) is still a matter of debate.

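### The surveillance definition of progression does not name regional lymph-node metastasis, and its rank against RECIST 1.0 is unstated, so nodal-only disease has no fixed classification in the primary endpoint

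*Protocol*

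**What the plan says.** The primary endpoint (section 7, Main study endpoint) is the time from enrolment to "first evidence of progression (surveillance group) or recurrence of disease (surgery group) or death from disease". No sites of recurrence are listed for the surgery group.

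Section 8 (Statistical Analysis) then defines the event in three steps:

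- A general sentence that is not limited to one group: "Progression/recurrence is defined according to Response Evaluation Criteria in Solid Tumors (RECIST"), version 1.0.
- A sentence for the surveillance group only: "progression is defined as the appearance of distant metastases and/or local signs of invasiveness (I.e. vascular or nearby organs invasion").
- A size rule: "The mere tumor size increasing will be not considered a sign of progression unless it reaches > 2 cm of maximum diameter".

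Events are judged "on the basis of treating physician-assessed tumor progression/recurrence". The protocol describes no central review.

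Among the secondary endpoints, tumour evolution is described as "development of symptoms, tumour growth, development of distant metastases and secondary pancreatic duct dilatation". The Background supports conservative management of small tumours partly by their "very low incidence of aggressive features such as lymph node involvement".

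**The concern.** Consider a patient under surveillance with a 15 mm primary who develops a new peripancreatic nodal metastasis. Under the surveillance sentence this is not a distant metastasis, it is not invasion of a vessel or a neighbouring organ, and the primary has not passed 2 cm. The abbreviation i.e. closes the description of local invasiveness; it does not introduce examples. A site that applies the sentence literally records no event. The evolution endpoint does not name the finding either, so neither outcome that describes the course under surveillance is certain to register it.

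The protocol itself cites nodal involvement as an example of aggressive behaviour whose rarity supports watching small tumours. An endpoint that need not register that feature can make progression-free survival under surveillance look better than it is. Risk-factor analyses of progression/recurrence, and the count of events that decides whether multivariate analysis is run, depend on the same classification.

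**Working it through.** There is no stated figure to reproduce, because the question is how a definition reads. The first step sets the texts side by side. The second gives a sense of scale.

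**1. How new regional nodal disease is classified**

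| Text | Surveillance group | Surgery group |
|---|---|---|
| Main study endpoint (section 7) | progression, sites not listed | recurrence, sites not listed |
| RECIST 1.0 sentence (section 8) | applies as written | applies as written |
| Surveillance sentence and size rule (section 8) | nodes not named | does not apply |
| Evolution endpoint (section 7, secondary) | nodes not named | nodes not named |

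The size rule sets a specific condition for growth under surveillance, so the surveillance text at least modifies the general sentence. The protocol does not say whether it replaces RECIST 1.0 or supplements it. If it replaces RECIST, nodal-only disease is not an event until a listed event or death from disease occurs. If it supplements RECIST, nodal-only disease may be an event; the protocol cites the criteria without reproducing them. Section 6.2 leaves surgery to the treating physician when follow-up findings change. A patient resected because of new nodes might therefore never reach a listed event, and the omission could be permanent rather than a delay.

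**2. Scale**

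Inputs from the protocol: at least 1000 patients (section 5.4); expected events 0-10% in the two groups, and multivariate analysis only with more than 30 events (section 8).

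- Expected events: 0% × 1000 = 0 to 10% × 1000 = 100.
- Rate at the threshold: 30 / 1000 = 3.0%.

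Assumptions, not in the protocol: 500 to 750 patients under surveillance; 0.5% to 2% with nodal-only disease; event counts that follow a Poisson distribution; the threshold applied to both groups together.

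- Events that depend on the reading: 500 × 0.5% = 2.5 to 750 × 2% = 15.

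Probability of more than 30 events, P(X > 30), with mean = other events + nodal-only events:

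| Other events expected | Nodal-only not counted | Counted, 500 under surveillance (0.5% to 2%) | Counted, 750 under surveillance (0.5% to 2%) |
|---|---|---|---|
| 20 (2%) | 0.01 | 0.05 to 0.45 | 0.09 to 0.77 |
| 30 (3%) | 0.45 | 0.63 to 0.94 | 0.71 to 0.99 |
| 40 (4%) | 0.94 | 0.97 to 1.00 | 0.98 to 1.00 |

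The reading matters most when other events lie near or somewhat below the threshold. At 4% it hardly changes whether the multivariate analysis is run.

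**The case against.** The strongest reply is the RECIST sentence. It stands directly before the surveillance definition, covers progression as well as recurrence, and is not confined to one group. A physician may count nodal disease through it. This stands in part: a reader might infer that such a patient is certainly recorded as progression-free, and the protocol does not support that. It does not remove the problem, because two unranked sentences can give different answers for the same patient and no central review is described to reconcile them.

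A second tempting inference is that the difference between groups biases surveillance against surgery. It does not stand. Section 8 says that the two groups will not be directly compared. That nodal relapse after surgery counts is also only the natural reading of an unrestricted term; the protocol does not spell it out.

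Third, the frequency may be very small. The Background describes nodal involvement as very uncommon at this size and reports no progression in observed patients with lesions under 2 cm. The documents give no nodal-only rate and no split between groups, so no particular understatement of the progression rate can be claimed.

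Fourth, it would go too far to say that nodal spread cannot be captured. CRF 4 records pathological findings, CT or MRI is mandatory at least every 12 months under section 6.2, and the content of CRF 2 is not shown.

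**Conclusion.** The point holds as a defect in the definition of the primary endpoint. The protocol fixes a surveillance-specific rule that does not name regional nodal metastasis, leaves its rank against RECIST 1.0 open, and repeats the omission in the evolution endpoint. The classification of nodal-only disease is therefore undetermined, may vary between treating physicians, and may differ between groups. Under the literal surveillance reading, progression-free survival in that group is overstated. Any risk-factor analysis that combines progression and recurrence, and the threshold of more than 30 events, are affected as well.

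The size cannot be derived from the documents. The figure of about 2.5 to 15 events rests wholly on the assumed nodal rate and the assumed number under surveillance. No planned between-group contrast is biased.

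**What to change.** In section 8:

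- Add new regional lymph-node metastasis, seen on the scheduled CT or MRI or proven histologically, to the surveillance definition of progression.
- State that it is an event in both groups.
- State that the surveillance sentence governs over RECIST 1.0 where the two differ.

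In section 7, add lymph-node metastases to the evolution endpoint. Confirm that CRF 2 captures the finding, and add an item if it does not. Report the components of the primary event separately.

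The criterion should not rest on receptor-positive nodes. After enrolment, Appendix 2 leaves 68Ga PET/CT to the treating physician, so detection would then vary with local practice.

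The cost is a wording change and at most one form item, using imaging already scheduled. The surveillance event rate may become slightly less favourable, and some reactive nodes may be called events. Reporting by component makes both visible.

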## 5.2 Inclusion Criteria

- Age > 18 years
- Individuals with asymptomatic sporadic NF-PNEN ≤ 2 cm
- Diagnosis has to be proven by a positive fine-needle aspiration (FNA) or by the presence of a measurable nodule on high-quality imaging technique (CT or MR) that is positive at ^68^Gallium DOTATOC-PET scan or Octreoscan.
- Patients who undergo surgery for NF-PNEN<2cm within 12 months. In these cases, diagnosis has to be proven by histological confirmation of NF-PNEN
- Informed consent

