**5.3 Exclusion Criteria**

- NF-PNEN > 2 cm of maximum diameter
- Presence of genetic syndrome (MEN1, VHL, NF)
- Presence of symptoms (specific symptoms suspicious of a clinical syndrome related to hypersecretion of bioactive compounds) or unspecific symptoms

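### Progression under surveillance has two rules with no stated precedence, and its 2 cm event line is also the entry limit, so measurement error near 20 mm can create primary events

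*Protocol*

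**What the plan says.** The primary endpoint (Section 7, Main study endpoint) is time from enrolment to "first evidence of progression (surveillance group) or recurrence of disease (surgery group) or death from disease". Progression is therefore the surveillance-group event.

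Section 8 defines the event in three consecutive sentences:

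- "Progression/recurrence is defined according to Response Evaluation Criteria in Solid Tumors (RECIST", version 1.0, with no group excepted.
- "In the surveillance group progression is defined as the appearance of distant metastases and/or local signs of invasiveness".
- "The mere tumor size increasing will be not considered a sign of progression unless it reaches > 2 cm of maximum diameter".

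Outcomes are judged "on the basis of treating physician-assessed tumor progression/recurrence". Section 5.2 admits "Individuals with asymptomatic sporadic NF-PNEN ≤ 2 cm" and Section 5.3 excludes "NF-PNEN > 2 cm of maximum diameter". Section 6.2 advises surveillance by MR, EUS or US every six months for two years and then yearly, with MRI or CT mandatory at least every 12 months. Section 8 expects event rates of 0-10% in the two groups. It lists size at diagnosis and growth during follow-up as the first two potential risk factors.

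**The concern.** There are two separate problems.

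First, RECIST and the surveillance-specific rule both claim the word progression, and no sentence ranks them. Two physicians could code the same patient differently on the only primary endpoint.

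Second, the event line and the entry line coincide. A lesion of exactly 20 mm is eligible, and the next reading of 21 mm is an event. No minimum change, repeat scan or constant imaging method is required. Part of the surveillance event rate may then reflect measurement variation in lesions enrolled close to the limit. Baseline size, a listed risk factor, is tied to the event by construction, because a larger lesion starts nearer the line. Growth during follow-up is likewise a risk factor for an event that growth can itself define.

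**Working it through.** **The plan's own figure.** The 0-10% rate comes from a cited systematic review, so it cannot be reproduced from the protocol. Whether that review counted crossing 2 cm as an event cannot be checked here.

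**Step 1: where the two rules disagree.** The protocol does not reproduce the RECIST criteria. I assume a relative-growth threshold r. With baseline diameter B, a relative rule fires at B(1 + r) and the fixed rule fires above 20 mm. They coincide at B = 20/(1 + r): 18.2 mm for r = 10%, 16.7 mm for 20%, 15.4 mm for 30%. At r = 20%:

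- 10 to 13 mm (+30%) is an event by relative growth only.
- 20 to 21 mm (+5%) is an event by the 2 cm line only.

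Any relative threshold produces some disagreement of this kind.

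**Step 2: one stable lesion.** Let T be the true diameter, with no growth and independent normal reading errors. The chance that one reading exceeds 20 mm is p = 1 − Φ((c − T)/SD), with c = 20 for continuous readings and c = 20.5 for whole millimetres. Over three scans the chance of at least one crossing is 1 − (1 − p)³. With whole-millimetre readings:

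| True size | SD 1 mm | SD 1.5 mm | SD 2 mm |
|---|---|---|---|
| 16 mm | 0% | 0.4% | 4% |
| 18 mm | 2% | 14% | 28% |
| 19 mm | 19% | 40% | 54% |
| 20 mm | 67% | 75% | 79% |

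Example: T = 20, SD = 1 gives p = 1 − Φ(0.5) = 0.309, and 1 − 0.691³ = 0.67.

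**Step 3: the surveillance cohort.** Assume T uniform on 5-20 mm and entry only if the baseline reading is 20 mm or less, which has probability 1 − p. The share with a false crossing is ∫(1 − p)[1 − (1 − p)³]dT / ∫(1 − p)dT. For baseline readings of 18-20 mm, the weight 1 − p is replaced by the chance that the baseline reading falls in that band. By numerical integration:

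| | SD 1 mm | SD 1.5 mm | SD 2 mm |
|---|---|---|---|
| All, continuous | 4.4% | 6.7% | 9.1% |
| All, whole mm | 2.8% | 5.1% | 7.4% |
| Baseline 18-20 mm, continuous | 33% | 40% | 44% |
| Baseline 18-20 mm, whole mm | 17% | 27% | 33% |

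**Step 4: effect of confirmation.** The chance of two consecutive readings above 20 mm among three is 2p² − p³. Put into the same integral, it gives 0.9% / 1.3% / 1.8% (continuous) or 0.3% / 0.7% / 1.1% (whole mm).

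**Step 5: knock-on effect.** Section 8 allows multivariate analysis only above 30 events. If all 1000 patients in Section 5.4 were under surveillance, a false-crossing share of 31/1000 = 3.1% would pass that trigger by itself. With fewer under surveillance, a larger share is needed.

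**The case against.** The strongest reply is that the sentences read naturally as a general rule followed by a specific one. On that reading the surveillance definition displaces RECIST, and the size sentence limits when growth counts. I agree that this is the likely intent. What is missing is a statement of precedence, which one clause would supply. A reader might infer that the rules cannot be reconciled, or that physicians will certainly apply different ones. The text supports neither inference.

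A reader might also infer that false crossings alone would equal or exceed the expected 0-10%. Letting true sizes run up to 23 mm gives about 7% / 10% / 13% over three scans. However, some 36% of those crossings come from lesions truly above 20 mm that were under-read at entry. Their later readings are correct; the entry reading was wrong. With true sizes capped at 20 mm, three scans stay below 10%. The share passes 10% only under harsher assumptions. With whole-millimetre readings and SD 2 mm, it is 10.2% over five scans for sizes 5-20 mm, and 11.4% over three scans if all lesions are 10-20 mm.

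Three further points limit the concern:

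- Disregarding growth below 2 cm, such as 8 to 16 mm, is a deliberate choice, and tumour growth is a secondary endpoint.
- The two groups are not to be directly compared, so no planned between-group test is biased.
- Sections 5.2 and 5.3 do not explicitly exclude metastases or invasion at baseline. A reader might take that as part of the same defect, but it is a separate eligibility question. The protocol gives no count for it, and the word appearance in Section 8 already implies a new finding.

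The shared entry and event line stands, as does the absence of a minimum increase or confirmation.

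**Conclusion.** The point holds. Precedence between the two definitions is unstated. Followed exactly, the surveillance rule makes one 20-to-21 mm reading a primary event. This is a consequence of what the protocol fixes, not of detail left for later.

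Under the stated assumptions, false crossings affect roughly 3% to 9% of surveillance patients over three scans, and 17% to 44% of those read at 18-20 mm at baseline. This could be a substantial part of the expected 0-10%, with the caveat that the event definition behind that range is not at hand. The direction follows from the text. The size depends on the assumed measurement SD, size mix, number of scans and independence of errors.

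It would go too far to say that the surveillance event rate will reflect near-limit enrolment rather than tumour behaviour. True growth, metastasis and invasion also contribute, and their rates are unknown.

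**What to change.** The changes concern how endpoint events are counted. They leave clinical decisions with the treating physician.

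1. Reconcile the Section 8 sentences: state that the surveillance-specific definition governs the surveillance group and that RECIST applies to recurrence after surgery.
2. Keep distant metastases, local invasiveness and death from disease as events. Count a diameter above 2 cm as a primary event only if the increase from the enrolment diameter exceeds a pre-stated measurement-error margin, or it is confirmed at the next scheduled CT or MRI, or both. The protocol should say which. Date a confirmed event at the first crossing.
3. Report unconfirmed crossings under the existing secondary endpoint on tumour growth. Add a sensitivity analysis of the primary endpoint without size-only events.

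The cost is mainly wording, with some consequences. There will be fewer primary events, and size events are ascertained one scan later. A handling rule is needed for crossings at a patient's last scan and for those followed by surgery before the next scan. Serial diameters must be recorded; Section 6.3 lists only the titles of the case record forms, so this needs checking.
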